## Appendix 1: Abbreviations

---

|           |                                                                          |
|-----------|--------------------------------------------------------------------------|
| AE        | Adverse Event                                                            |
| ALP       | Alkaline phosphatase                                                     |
| ALT       | Alanine transaminase                                                     |
| ANC       | Absolute Neutrophil Count                                                |
| AR        | Adverse Reaction                                                         |
| AST       | Aspartate aminotransferase                                               |
| AUC       | Area Under the Curve                                                     |
| CI        | Chief Investigator                                                       |
| CLS       | Country Lead Site                                                        |
| CR        | Complete response                                                        |
| CRF       | Case Report Form                                                         |
| CTA       | Clinical Trial Authorisation                                             |
| CTAAC     | Clinical Trials Advisory & Awards Committee                              |
| CTCAE     | National Cancer Institute Common Terminology Criteria for Adverse Events |
| CTSA      | Clinical Trial Site Agreement                                            |
| DPA       | Data Protection Act                                                      |
| ECG       | Electrocardiogram                                                        |
| ECOG      | Eastern Cooperative Oncology Group                                       |
| EGF       | Epidermal growth factor                                                  |
| EGFR      | Epidermal growth factor receptor (ErbB1)                                 |
| EGFR vIII | Epidermal growth factor receptor variant III                             |
| EMA       | European Medicines Agency                                                |
| EudraCT   | European Clinical Trials Database                                        |
| FBC       | Full Blood Count                                                         |
| FDA       | US Food and Drug Administration                                          |
| GBM       | Glioblastoma                                                             |
| GFR       | Glomerular Filtration Rate                                               |
| Hb        | Haemoglobin                                                              |
| IB        | Investigators Brochure                                                   |
| ICH GCP   | International Conference of Harmonisation-Good Clinical Practice         |
| IDH       | Isocitrate dehydrogenase                                                 |
| IDMC      | Independent Data Monitoring Committee                                    |
| ILD       | Interstitial lung disease                                                |
| IMP       | Investigational Medicinal Product                                        |
| INR       | International Normalised Ratio                                           |
| ISRCTN    | International Standard Randomised Controlled Trial Number                |
| ITSC      | Independent Trial Steering Committee                                     |
| IV        | Intravenous                                                              |
| IWRS      | Interactive web-based recognition system                                 |
| LDH       | Lactate Dehydrogenase                                                    |
| LFT       | Liver Function Tests                                                     |
| LLN       | Lower Limit of Normal                                                    |
| MGMT      | O  -methylguanine-DNA methyltransferase                      |
| MTOR      | Mammalian target of rapamycin                                            |
| MRC       | Medical Research Council                                                 |
| MRI       | Magnetic Resonance Image                                                 |
| MHRA      | Medicines and Healthcare products Regulatory Agency                      |
| NCRI      | National Cancer Research Institute                                       |
| NCRN      | National Cancer Research Network                                         |
| NRES      | National Research Ethics Service                                         |

---

---

|         |                                                   |
|---------|---------------------------------------------------|
| NSCLC   | Non small cell lung cancer                        |
| OS      | Overall Survival                                  |
| PD      | Progressive Disease                               |
| PDGFR   | Platelet derived growth factor receptor           |
| PFS     | Progression Free Survival                         |
| PI      | Principal Investigator                            |
| PO      | By mouth                                          |
| PPE     | Palmar plantar erythrodysesthesia                 |
| PR      | Partial Response                                  |
| PTEN    | Phosphatase and tensin homolog                    |
| RANO    | Response Assessment for Neuro-Oncology            |
| REC     | Research Ethics Committee                         |
| RPLS    | Reversible posterior leucoencephalopathy syndrome |
| SAE     | Serious Adverse Event                             |
| SD      | Stable Disease                                    |
| SmPC    | Summary of Product Characteristics                |
| SSA     | Site Specific Assessment                          |
| SUSAR   | Suspected Unexpected Serious Adverse Reaction     |
| TKI     | Tyrosine kinase inhibitor                         |
| TMF     | Trial Master File                                 |
| TMG     | Trial Management Group                            |
| UCL CTC | CR UK and UCL Cancer Trials Centre                |
| ULN     | Upper Limit of Normal                             |
| ULRR    | Upper limit of reference range                    |
| UPC     | Urine protein creatinine                          |
| VEGF    | Vascular endothelial growth factor                |
| VEGFR   | Vascular endothelial growth factor receptor       |
| WBC     | White Blood Cells                                 |

## Appendix 2: Recommended Skin Care products

### Skin care products Product information (Schwandt A et al. 2009)

| Skin care products                                                     | Product information                                                                                 |
|------------------------------------------------------------------------|-----------------------------------------------------------------------------------------------------|
| Cetaphil skin cleanser; Aveeno® shower gel                             | Non-deodorant, non-fragrant body washes                                                             |
| Udderly Smooth® udder cream                                            | Allantoin, dimethicone                                                                              |
| Udderly Smooth® extra care cream                                       | Allantoin, dimethicone, 10% urea                                                                    |
| Aveeno® skin relief moisturizing cream                                 | Natural colloidal oatmeal; dimethicone                                                              |
| Norwegian Formula: soothing relief anti-itch moisturizer by Neutrogena | Dimethicone 1%, camphor 0.1%, and lidocaine                                                         |
| Norwegian Formula: foot cream by Neutrogena                            | Ceterayl alcohol, dimethicone, menthol and urea                                                     |
| Bag Balm®                                                              | 8-hydroxyquinoline sulfate 0.3% in a petrolatum lanolin base; eucalyptus                            |
| Eucerin® cream                                                         | Mineral oil, lanolin                                                                                |
| Eucerin® dry skin therapy                                              | Urea and alpha hydroxy acid                                                                         |
| Aquaphor® healing ointment                                             | 41% petrolatum                                                                                      |
| Xenaderm® ointment                                                     | Balsam peru, castor oil, trypsin                                                                    |
| Corn Huskers Lotion®                                                   | Calcium alginate; non-oily moisturizer                                                              |
| Biafine® cream                                                         | Water-based emulsion for radiation dermatitis or abrasions                                          |
| Gold Bond® triple action relief cream                                  | 5% dimethicone, 0.15% menthol, aloe, vitamin E                                                      |
| Gold Bond® ultimate healing lotion                                     | 5% dimethicone, jojoba esters, aloe                                                                 |
| Gold Bond® anti-itch cream                                             | 1% pramoxine HCL, 1% menthol                                                                        |
| Kerasal™                                                               | 5% salicylic acid: softens skin 10% urea: exfoliates and moisturizes                                |
| Keralac™ cream                                                         | 50% urea: exfoliates and moisturizes vitamin E, lactic acid, zinc                                   |
| Keralac™ lotion                                                        | 35% urea: exfoliates and moisturizes vitamin E, lactic acid, zinc                                   |
| Carmol® 40                                                             | 40% urea                                                                                            |
| Miracle Foot Repair® cream                                             | 60% aloe, 0.1% menthol                                                                              |
| Regenecare® HA                                                         | 2% lidocaine, humectant (moisturizer), aloe vera extract, hyaluronic acid (anti-inflammatory agent) |
| Lidocaine topical                                                      | 2% lidocaine                                                                                        |
| Lidamantle®                                                            | 3% lidocaine HCL                                                                                    |
| Lidamantle HC®                                                         | 3% lidocaine HCL, 0.5% hydrocortisone acetate                                                       |
| Pramocaine HCL                                                         | 1% pramoxine hydrochloride                                                                          |
| Tetracaine jelly                                                       | 2% lidocaine                                                                                        |

## Appendix 3: Recommended Oral Care products

### Oral care products

| Cleansers and rinses                             | Product information                             |
|--------------------------------------------------|-------------------------------------------------|
| Salt water rinse                                 |                                                 |
| Salt and baking soda rinse                       |                                                 |
| Biotine® rinse                                   | Bioactive enzymes                               |
| Chlorhexidine gluconate 0.12%                    | Antimicrobial mouth rinse                       |
| Toothpastes                               |                                                 |
| Sensodyne® toothpaste                            | Potassium nitrate to reduce painful sensitivity |
| Children's toothpaste                            | Flavoring is milder and burns less              |
| Rinses for comfort and mucosal protection |                                                 |
| Rincinol™ PRN                                    | Aloe vera rinse                                 |
| Gelclair® bioadherent oral gel                   | Hydrates, soothes, and protects oral mucosa     |
| Lidocaine Viscous                                | 2% lidocaine hydrochloride solution             |
| Lip protectants                           |                                                 |
| Blistex®                                         | Dimethicone                                     |
| Burt's Bees®                                     | Beeswax, oils, lanolin                          |
| Carmex®                                          | Menthol, camphor, phenol                        |
| Zim's Crack Creme®                               | Arnica                                          |

## Appendix 4: Drugs thought to significantly interact with CYP450 enzymes

These drugs are recommended to be avoided in combination with cediranib and/or gefitinib, and for 2 weeks prior to starting trial treatment.

| Enzyme                  | Potent Inhibitors*                                                                                                                                                        | Potent Inducers**                                                                                        | Substrates†                                                                                                                                      |
|-------------------------|---------------------------------------------------------------------------------------------------------------------------------------------------------------------------|----------------------------------------------------------------------------------------------------------|--------------------------------------------------------------------------------------------------------------------------------------------------|
| CYP1A2                  | Amiodarone,
cimetidine,
ciprofloxacin,
fluvoxamine                                                                                                               | Carbamazepine ,
phenobarbital,
rifampin,
tobacco                                                | Caffeine,
clozapine,
theophylline                                                                                                          |
| CYP2C9                  | Amiodarone,
fluconazole,
fluoxetine,
metronidazole,
ritonavir,
trimethoprim /sulfamethoxazole                                                              | Carbamazepine,
phenobarbital,
phenytoin,
rifampin                                               | Carvedilol,
celecoxib,
glipizide,
ibuprofen,
irbesartan,
losartan                                                                 |
| CYP2C19                 | Fluvoxamine,
isoniazid,
ritonavir                                                                                                                                   | Carbamazepine,
phenytoin,
rifampin                                                                 | Omeprazole,
phenobarbital,
phenytoin                                                                                                       |
| CYP2D6                  | Amiodarone,
cimetidine,
diphenhydramine,
fluoxetine,
paroxetine,
quinidine,
ritonavir,
terbinafine                                                   | No significant inducers                                                                                  | Amitriptyline,
carvedilol,
codeine,
donepezil,
haloperidol,
metoprolol,
paroxetine,
risperidone,
tramadol                |
| CYP3A4
and
CYP3A5 | Clarithromycin,
diltiazem,
erythromycin,
grapefruit juice ,
itraconazole,
ketoconazole,
nefazodone,
ritonavir,
telithromycin,
verapamil | Carbamazepine,
Hypericum perforatum
(St. John's wort),
phenobarbital,
phenytoin,
rifampin | Alprazolam,
amlodipine,
atorvastatin,
cyclosporine,
diazepam,
estradiol,
simvastatin,
sildenafil,
verapamil,
zolpidem |

\* These will slow down substrate drug metabolism and increase drug effect.

\*\* These will speed up substrate drug metabolism and decrease drug effect

† Exposure, pharmacological action and toxicity may be increased in combination with cediranib and/or gefitinib

This list is not exhaustive and a similar restriction will apply to other agents that are known to strongly induce, inhibit CYP450 enzyme activity or require CYP450 for metabolism. For an extensive list including less significant interactions see <http://medicine.iupui.edu/clinpharm/ddis/table.asp>.

Table compiled from: *Lynch T, Price A. (2007) The effect of cytochrome P450 metabolism on drug response, interactions, and adverse effects. Am Fam Physician. Aug 1;76(3):391-6.*

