### 5.1.2 Exclusion Criteria

Any of the following is regarded as a criterion for exclusion from the study:

- Patients on enzyme-inducing anti-epileptic drugs (see [section 7.5](#)) within 2 weeks prior to study enrolment. Note: Patients are eligible if they switched to non-enzyme inducing agents and discontinued enzyme-inducing agents for more than or equal to 2 weeks prior to randomisation
- Inadequate bone marrow reserve as demonstrated by an absolute neutrophil count  $\leq 1.5 \times 10^9$  /L or platelet count  $\leq 100 \times 10^9$  /L or requiring regular blood transfusions to maintain haemoglobin  $>9\text{g/dL}$
- Serum bilirubin  $\geq 1.5 \times \text{ULRR}$  (except for patients with known documented cases of Gilbert's Syndrome)
- ALT or AST  $\geq 5 \times \text{ULRR}$
- Serum creatinine  $>1.5 \times \text{ULRR}$  or a creatinine clearance of  $\leq 50\text{mL/min}$  calculated by Cockcroft-Gault

- Greater than +1 proteinuria on two consecutive dipsticks taken no less than 1 week apart unless urinary protein <1.5g in a 24 hr period or UPC (Urine Protein: Creatinine) ratio <1.5
- History of significant gastrointestinal impairment, as judged by the investigator, that would significantly affect the absorption of cediranib or gefitinib, including the ability to swallow the tablet whole
- Patients with a history of poorly controlled hypertension with resting blood pressure >150/100mmHg in the presence or absence of a stable regimen of anti-hypertensive therapy, or patients who are requiring maximal doses of calcium channel blockers to stabilise blood pressure
- Any evidence of severe or uncontrolled diseases (e.g. unstable or uncompensated respiratory, cardiac, hepatic or renal disease)
- Unresolved toxicity >CTC AE grade 1 from previous anti-cancer therapy (including radiotherapy) except alopecia (if applicable)
- Mean QTc with Bazetts correction >470msec in screening ECG or history of familial, long QT syndrome (see Appendix 7)
- Cardiac ventricular arrhythmias requiring anti-arrhythmic therapy
- Significant haemorrhage (>30mL bleeding/episode in previous 3 months) or haemoptysis (>5mL fresh blood in previous 4 weeks)
- Recent (<14 days) major surgery or brain biopsy. Recent craniotomy (<28 days) prior to first dose, or a surgical incision that is not fully healed
- Pregnant or breast-feeding women or women of childbearing potential with a positive pregnancy test prior to receiving study medication (see [section 5.1.3](#))

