| Mild to moderate hypertension:

BP 140/90 mmHg on 2 consecutive occasions >24 hours apart

OR

Increase in diastolic pressure by $\geq 20$ mmHg or to $\geq 100$ mmHg or increase in systolic pressure to $\geq 150$ mmHg | 
 
1. Repeat reading at least 1 hour later. If isolated increase, increase BP monitoring to weekly by health professional or daily home monitoring. Continue all study medication at the same dose.
 
2. If confirmed by second reading, continue all study medication at the same dose and initiate monotherapy with a long acting dihydropyridine calcium-channel blocker (e.g. nifedipine, amlodipine, felodipine) at low dose.
 
3. If calcium channel blocker is contraindicated, use thiazide diuretic or angiotensin converting enzyme inhibitors or angiotensin receptor blockers first line.
 
4. Monitor BP 3 weekly by health professional until it stabilises.
 
5. If BP >140/90 mmHg after 3 weeks INCREASE the first agent to the full dose and consider adding an additional agent in combination (e.g., selective <math>\beta</math>-blocker, thiazide diuretic, angiotensin converting enzyme inhibitors or angiotensin receptor blockers).
 
6. If BP >140/90 mmHg after a further 3 weeks, add an additional agent if the patient is only on one new agent or increase to full doses of the 2-drug combination.
 
7. If BP >160/95 mmHg and is static or increasing after a further 7 days, temporarily stop cediranib and continue anti-hypertensive therapy under close supervision.
 
8. Restart cediranib at the same dose (with maintenance anti-hypertensive therapy) when BP <math>\leq 140/90</math> mmHg. Monitor BP every week until BP stabilised.
 
9. If BP >160/95 mmHg and is static or increasing after 7 days, temporarily stop cediranib and continue anti-hypertensive therapy under close supervision.
 
10. Restart cediranib but at 1 dose lower than the starting dose when BP <math>\leq 140/90</math> mmHg. Monitor BP every week by health professional until BP stabilised.
 
11. If BP increases to >160/95 mmHg, temporarily stop cediranib and continue anti-hypertensive therapy under close supervision
 
12. Restart cediranib but at 2 doses lower than the starting dose when BP <140/90 mmHg. Monitor BP every week until steady state is BP stabilised
 
13. If BP increases to >160/95 mmHg after dose reduction to 15 mg od, despite anti-hypertensive therapy, permanently stop cediranib.
 
 |

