| Severe hypertension:

Increase in diastolic pressure to $\geq 110$ mmHg or increase in systolic pressure to $\geq 180$ mmHg on 2 readings >1 hour apart | 
 
1. Temporarily stop cediranib and consider if hospitalisation is necessary.
 
2. Initiate treatment with a 2-drug combination including a calcium channel blocker licensed for use in severe hypertension, tailored to the patient's underlying conditions and previous anti-hypertension treatment.
 
3. If there is evidence of target-organ damage, intravenous therapy should be considered while continuing oral therapy.
 
4. Nitrates may adversely affect the therapeutic mechanism of action of cediranib but should be used if clinically indicated.
 
5. Restart cediranib at 1 dose lower than the starting dose when BP <140/90 mmHg. Monitor BP every 3 to 7 days until steady state is BP stabilised
 
6. If BP increases to >160/95 mmHg, temporarily stop cediranib and continue anti-hypertensive therapy under close supervision.
 
7. Restart cediranib at 2 doses lower than the starting dose when BP <140/90 mmHg. Monitor BP every week until steady state is BP stabilised.
 
8. If BP increases to >160/95 mmHg after dose reduction to 15 mg od, despite anti-hypertensive therapy, permanently stop cediranib.
 
 |

The development of hypertension in patients treated with cediranib is generally an early event, usually occurring in the first 4 weeks of treatment. In a minority of patients hypertension can also occur later in a treatment schedule.

The rigorous monitoring of BP and adherence to the hypertension management guidelines are necessary in order to achieve optimal hypertension control. Patients on prior anti-hypertension therapy may be particularly at risk of developing moderate or severe hypertension on cediranib. Therefore, patients with pre-existing hypertension or on anti-hypertension medications are likely to benefit from having their BP management optimised before starting cediranib.

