For all BP thresholds described in this protocol, a trigger level is considered to be met if either the systolic and/or diastolic pressure reaches the threshold. If the threshold is recorded at home, it must be confirmed by a healthcare professional as defined above before commencing any treatment. CLEAR reasons for progressing to the next step in the management protocol must be documented. When managing mild to moderate hypertension, the following principles should be noted:

- Cediranib may cause rapid increases in BP in some patients
- Calcium-channel antagonists are the first line agents of choice
- Increase anti-hypertensives to maximum doses and add additional agents as required.
- It is recommended that no more than 2 drugs are added in a 48-hour period before temporarily stopping cediranib.

The following cautions and contraindications should be noted:

- Calcium-channel blockers: use with caution in patients with tachyarrhythmias, aortic stenosis, unstable angina or congestive cardiac failure and may cause headache
- Short-acting non-dihydropyridines such as diltiazem or verapamil should be avoided since they may precipitate abrupt fall in BP and increase risk of myocardial ischaemia, infarction or stroke
- Beta-blockers: contraindicated in patients with asthma, chronic obstructive pulmonary disease and A-V block; they should be used with caution in patients with peripheral vascular disease and glucose intolerance and may cause fatigue
- If diuretics are to be used, thiazides rather than loop diuretics are recommended

A record of the management of hypertension will be maintained.

CTCAE grade 3 should NOT be assigned to hypertension AEs on the basis of the number of drugs used according to this protocol to treat mild-moderate hypertension since this is a proactive treatment approach. CTCAE grade 3 should be assigned **if hypertension is not controlled after 7 days of per-protocol anti-hypertensive therapy.**

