#### **7.4.1.7 Reversible posterior leukoencephalopathy syndrome**

Reversible posterior leukoencephalopathy syndrome (RPLS) is a rare syndrome affecting vascular endothelial cells in the brain that may lead to capillary leak and oedema, and was first described in 1996 (Hinchey et al. 1996). It has been associated with a number of conditions, including renal failure, hypertension, fluid retention, and the use of cytotoxic or immunosuppressive drugs. It has also been reported rarely in association with the use of VEGF inhibitors including bevacizumab and sunitinib. Cases of Magnetic Resonance Imaging (MRI)-documented RPLS have rarely been reported in patients receiving cediranib in clinical studies.

The syndrome can present in a variety of non-specific ways, including headache, seizures, lethargy, confusion, blindness and other visual and neurological disturbances. Hypertension may be present, but is not necessary for the diagnosis of RPLS. MRI is the most sensitive imaging modality to detect RPLS and is recommended in suspected cases to confirm the diagnosis. RPLS is reversible upon removal of any possible precipitating factors and control of hypertension.

Active management of hypertension according to the hypertension management guidelines in this section may be expected to reduce the incidence of RPLS. However, if any case of RPLS occurs that is confirmed by imaging (CT or MRI), cediranib should be immediately discontinued in addition to any other measures to alleviate symptoms and control blood pressure.

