### l) Time between screening and baseline

A maximum of 14 days between screening and baseline is permitted. However for patients switching from enzyme inducing anti-epileptic drugs to non-enzyme inducing anti-epileptic drugs, this can be extended to a maximum of 21 days before baseline (as a wash-out period of 2 weeks is required. See 5.1.2 Exclusion criteria). Screening assessments must be performed within 7 days before randomisation, as per [section 5.2](#) (pre-randomisation evaluation). **If more than 14 days pass between screening and baseline, the randomisation form must be updated with pre-randomisation tests completed within 14 days of the baseline visit and this reassessed for eligibility at UCL CTC before the patient proceeds with the baseline assessments.**

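### Appendix 4 advises against antihypertensives, amlodipine among them, that Table 7 tells sites to use with study drug continued; nothing reconciles the two, and every pointer to the list is wrong

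*Protocol*

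**What the plan says.** **The avoid list.** Appendix 4 states: "These drugs are recommended to be avoided in combination with cediranib and/or gefitinib, and for 2 weeks prior to starting trial treatment". In the CYP3A4/3A5 row the substrates column begins "Alprazolam, amlodipine, atorvastatin". The substrates columns also contain losartan and irbesartan (CYP2C9), metoprolol (CYP2D6) and carvedilol (both). A footnote warns that exposure to a substrate, and its toxicity, may rise with the trial drugs. The closing note applies a similar restriction to unlisted agents that depend on CYP450 for their metabolism.

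**The hypertension plan.** For confirmed mild to moderate hypertension, Table 7 step 2 says to "continue all study medication at the same dose and initiate monotherapy with a long acting dihydropyridine calcium-channel blocker (e.g. nifedipine, amlodipine, felodipine", at low dose. Step 3 allows angiotensin receptor blockers, among others, if a calcium-channel blocker is contraindicated. Step 5 allows selective beta-blockers and angiotensin receptor blockers as add-ons. The principles after the table state: "Calcium-channel antagonists are the first line agents of choice".

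**Before treatment.** Section 7.4.1.4 says that "patients with pre-existing hypertension or on anti-hypertension medications are likely to benefit from having their BP management optimised before starting cediranib". Section 5.1.2 excludes poorly controlled hypertension above 150/100 mmHg and "patients who are requiring maximal doses of calcium channel blockers to stabilise blood pressure".

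**Softening text.** Section 7.5 puts drugs that need P450 for metabolism on its caution list, from 2 weeks before the first dose, and allows them where essential for treatment. Section 7.4.3.2 explains that ciprofloxacin, also in Appendix 4, is given while study medication is stopped.

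**The concern.** The same drug, in the same patient taking study medication, gets opposite default advice: avoid it (Appendix 4), or start it as a routine first step (Table 7). A site reading Appendix 4 literally could withhold a named first-line agent. It could also hesitate over continuing that agent in an eligible patient already controlled on it.

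Blood pressure control matters in this trial. Table 7 interrupts, reduces or permanently stops cediranib when pressure stays above or returns above 160/95 mmHg. Section 7.4.1.4 says hypertension usually appears in the first 4 weeks of cediranib. Section 7.4.1.7 adds, on reversible posterior leukoencephalopathy syndrome: "Active management of hypertension according to the hypertension management guidelines in this section may be expected to reduce the incidence of RPLS". Instructions that bear on both safety and time on treatment should not point in two directions.

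**Working it through.** No arithmetic applies: the point depends on no sample size, power or event count. The check is to set the texts side by side.

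| Drug or class | Appendix 4 | Hypertension plan, section 7.4.1.4 | Agreement |
|---|---|---|---|
| Amlodipine | Listed, CYP3A4/3A5 substrate | Named example at step 2, study drug continued | Conflict |
| Angiotensin receptor blockers | Losartan and irbesartan listed, CYP2C9 substrates | Step 3 alternative, step 5 add-on | Conflict |
| Selective beta-blockers | Metoprolol listed, CYP2D6 substrate | Step 5 add-on | Conflict |
| Nifedipine, felodipine | Not listed; caught by the closing note if they need CYP450 for metabolism | Named examples at step 2 | Unclear |
| Diltiazem, verapamil | Listed | To be avoided | Agree |

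The protocol does not assign losartan, irbesartan and metoprolol to classes; that is ordinary pharmacology. Carvedilol is also listed, but it is not usually called selective, so the overlap is not rested on it.

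**Is the conflict resolved elsewhere?**

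1. *Ciprofloxacin.* Its note works because study drug is stopped. That reasoning cannot carry over to Table 7 step 2, which continues study drug.
2. *Section 7.5.* The allowance for essential drugs is general. It mentions neither Table 7 nor any antihypertensive.
3. *Section 5.1.2, Restrictions.* Drugs affecting renal function may be continued if already in use before entry without renal effect. The P450 item has no matching allowance.

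**Pre-treatment period.** A patient controlled on non-maximal amlodipine is not excluded by the hypertension criterion, and section 7.4.1.4 favours optimising pressure before cediranib. Appendix 4 advises against amlodipine for the 2 weeks before treatment. The advice conflicts here too.

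**Pointers to the list.** Section 5.1.2 (Restrictions), section 7.4.3.2 and section 7.5 each cite Appendix 3, which is oral care products. The CYP450 list is Appendix 4, so 3 of 3 are wrong. The same one-number shift affects skin care (sections 7.4.1.5 and 7.4.2.1 cite Appendix 1; it is Appendix 2) and oral care (section 7.4.1.6 cites Appendix 2; it is Appendix 3).

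**The case against.** The best defence is that the texts can be read together. Appendix 4 only recommends. Section 7.5 separates forbidden drugs from drugs to be used with caution, and P450 substrates fall in the second group. It also leaves medication needed for a patient's safety to the investigator, and section 7.4.1.4 calls adherence to the hypertension guidance necessary for optimal control. An antihypertensive started under Table 7 fits the essential-treatment route. The 2-week caution in section 5.1.2 covers only inducers and inhibitors, whereas amlodipine is listed only as a substrate.

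Much of this stands. It shows that a site can comply, and it keeps the point minor. It does not remove the conflict. An exception for essential use is a poor fit for a routine low-dose first step, and section 7.5, unlike section 5.1.2, does extend its 2-week caution to drugs that need P450 for metabolism. Choosing nifedipine or felodipine does not clearly help either, because of the closing note in Appendix 4.

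The wrong pointers are clerical: the contents list and appendix titles are correct, and the right list directly follows the oral-care appendix.

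A reader might infer that the 2-week advice makes screening unworkable, since "A maximum of 14 days between screening and baseline is permitted". It does not. A 14-day avoidance fits a 14-day window, Appendix 4 is not an eligibility criterion, and section 8.2(l) provides for updated tests when the interval is longer.

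**Conclusion.** The point holds as an inconsistency in default advice, of low severity. It covers amlodipine and at least two further antihypertensive classes offered in Table 7, and all three references to the list are wrong.

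Three stronger readings are not supported:

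- *The protocol forbids its own first-line treatment.* It does not; section 7.5 leaves a route open.
- *A countable share of the 112 patients is affected.* The protocol gives no hypertension rate. Even patients who reach step 2 could receive another named drug, or amlodipine as essential treatment.
- *The trial result is at risk.* The Appendix 4 footnote on substrates concerns exposure to the substrate, not to the trial drugs. Both arms receive cediranib under the same hypertension plan. No effect on the primary analysis follows.

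The conclusion rests on the text alone, apart from the drug-class assignments noted above.

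**What to change.** - Add one sentence to Appendix 4 and to section 7.5: antihypertensives started or continued under section 7.4.1.4 (dihydropyridines including amlodipine, angiotensin receptor blockers, selective beta-blockers) are exempt from the avoidance and 2-week advice, under the blood pressure monitoring Table 7 already requires.
- State in the same place that diltiazem and verapamil remain to be avoided, as section 7.4.1.4 says. Leave the advice for drugs outside this exemption unchanged.
- Change Appendix 3 to Appendix 4 in section 5.1.2 (Restrictions), section 7.4.3.2 and section 7.5.
- As clerical corrections, change Appendix 1 to 2 in sections 7.4.1.5 and 7.4.2.1, and Appendix 2 to 3 in section 7.4.1.6.

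Deleting amlodipine from Table 7 alone would not be enough: the overlap with angiotensin receptor blockers and beta-blockers, and the closing note on other CYP450-metabolised agents, would remain.

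The cost is a short exemption in two places and six corrected references, with no added visits, tests or treatment interruptions.
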